## Abstract

**Introduction:**

Fractures of the odontoid process frequently result from low impact falls in frail or older adults. These are increasing in incidence and importance as the population ages. In the UK, odontoid fractures in older adults are usually managed in hard collars to immobilise the fracture and promote bony healing. However, bony healing does not always occur in older adults, and bony healing is not associated with quality of life, functional, or pain outcomes. Further, hard collars can cause complications such as skin pressure ulcers, swallowing difficulties and difficulties with personal care. We hypothesise that management with no immobilisation may be superior to management in a hard collar for older or frail adults with odontoid fractures.

**Methods and analyses:**

This is the protocol for the Duration of External Neck Stabilisation (DENS) trial—a non-blinded randomised controlled trial comparing management in a hard collar with management without a collar for older (≥65 years) or frail (Rockwood Clinical Frailty Scale ≥5) adults with a new odontoid fracture. 887 neurologically intact participants with any odontoid process fracture type will be randomised to continuing with a hard collar (standard care) or removal of the collar (intervention). The primary outcome is quality of life measured using the EQ-5D-5L at 12 weeks. Secondary outcomes include pain scores, neck disability index, health and social care use and costs, and mortality.

**Ethics and dissemination:**

Informed consent for participation will be sought from those able to provide it. We will also include those who lack capacity to ensure representativeness of frail and acutely unwell older adults. Results will be disseminated via scientific publication, lay summary, and visual abstract. The DENS trial received a favourable ethical opinion from the Scotland A Research Ethics Committee (21/SS/0036) and the Leeds West Research Ethics Committee (21/YH/0141).

**Trial registration number:**

NCT04895644.

Strengths and limitations of this studyThe Duration of External Neck Stabilisation (DENS) trial is a multicentre non-blinded randomised controlled trial comparing the use of hard collars with no immobilisation.The primary outcome measure (EQ-5D-5L) is a quality of life measure relevant to the older or frail population.Health economic analysis and embedded qualitative study methods assess the wider implications of collar use in the older or frail population.Inclusion of all odontoid process fracture types, frail patients and those with cognitive impairment will ensure the results are applicable to these populations.The DENS trial does not directly compare surgical fixation and no immobilisation due to the preference for non-surgical management for older or frail patients in the UK.

## Introduction

### Background and rationale

Odontoid process (dens) fractures occur following low impact falls in frail and older people, and are increasing in incidence as the population ages.^1–3^ The Trauma Audit and Research Network database identified at least 1700 odontoid fractures each year in England and Wales, 85% in people over 65 years. One-year mortality following an odontoid fracture is 20%–50%, similar to or higher than following a hip fracture, likely reflecting the underlying frailty and health status of those at risk of low impact falls.^4–7^

In the UK, 85%–90% of frail or older people with a new odontoid fracture are managed non-operatively, most with 6–12 weeks immobilisation in a hard collar.^8–10^ This aims to promote bony fusion and prevent neurological deterioration or instability pain.^1 5 11^ However, hard collars only restrict 40%–50% of neck movements,^12 13^ and bony fusion rates of 20%–80% are variable across fracture types, management, age and frailty.^1 5 11 14–18^ Further, bony fusion may not be associated with pain, quality of life (QoL), mortality or functional outcomes in older people,^8 19 20^ and late neurological deterioration is very rare.^5 11 21^ Hard collars can cause skin pressure ulcers and difficulties with swallowing, breathing and personal care, all of which can affect QoL.^10 22^ Additional health and social care input is often required to assist patients with activities of daily living. If fibrous union, or lack of bony fusion is an acceptable outcome and hard collars can negatively impact QoL, then management of an odontoid fracture with a hard collar may be causing unnecessary harm and negatively impacting on QoL in a group for whom the short to medium term QoL may be more important than long term outcomes.

Spinal surgeons responding to a UK survey variably reported managing odontoid fractures without any immobilisation or removing hard collars in frail or older patients who were unable to tolerate a collar, had a short life expectancy or suffered complications.^10^ Ninety percent supported randomisation to management with or without a collar to determine optimum treatment.^10^ Further, feedback from patients managed in collars supports exploring whether collars are necessary for odontoid process fractures.

The Duration of External Neck Stabilisation (DENS) trial will test the hypothesis that management of odontoid process fractures without immobilisation is associated with improved QoL compared with management in a hard collar for 12 weeks.

### Aims and objectives

The primary aim is to determine the difference in QoL measured using the EQ-5D-5L (EuroQol 5 dimension instrument with 5 levels) at 12 weeks between frail or older patients with odontoid process fractures managed with a hard collar (standard care) or without any immobilisation (intervention).

Secondary aims include assessing differences in neck pain, functional recovery, complications, radiological findings, mortality and overall healthcare use and costs, up to 1 year postinjury.

A nested qualitative study will explore trial recruitment experiences from the perspectives of patients, carers, and healthcare professionals, and explore adherence to group allocation. Findings from the qualitative study will inform recruitment and consent procedures and aid interpretation of trial results.

## Methods and analysis

### Study design

This manuscript has been prepared in accordance with the SPIRIT checklist. The DENS trial is a non-blinded randomised controlled trial with a nested qualitative study comparing early hard collar removal (intervention) with treatment in a hard collar for 12 weeks (standard care) in older or frail adults with a new odontoid process fracture. Figure 1 shows the trial flow chart. The study will recruit from November 2021 to December 2023.

**Figure 1 F1:**
[figure not shown]
DENS trial flow chart. C-spine, cervical spine; CTU, Clinical Trials Unit; DENS, Duration of External Neck Stabilisation; DISH, diffuse idiopathic skeletal hyperostosis; NDI, Neck Disability Index; RCT, randomised controlled trial; VAS, Visual Analogue Scale; OPD, Outpatient Department; EQ-5D-5L, EuroQol 5 dimension instrument 5 level version.

### Study eligibility

#### Inclusion criteria

Aged ≥65 years, or Rockwood Clinical Frailty Scale (CFS) of ≥5 (at least mildly frail: help needed in high order instrumental activities of daily living).^23^Recent odontoid process fracture of any type^24^ secondary to low impact trauma (any degree of fracture angulation, displacement or canal narrowing).History of recent trauma (within 3 weeks).Recruited within 3 weeks of injury.Determined by consultant spinal surgeon as suitable for standard treatment in hard collar or treatment without a collar.

#### Exclusion criteria

Fracture sustained in a high-impact injury.New neurological deficit attributable to the fracture.Unable to tolerate a hard collar.Additional (non-odontoid process) cervical spine fracture not suitable for management without a hard collar.Underlying condition with risk of spinal instability (eg, ankylosing spondylitis).Fracture suspected to be older than 3 weeks at the time of assessment.Not expected to survive to hospital discharge.

A consultant radiologist report of an odontoid process fracture on CT and confirmation of eligibility by a consultant spinal surgeon (orthopaedic or neurosurgical) is required. Patients with additional cervical spine fractures are eligible provided the consultant spinal surgeon determines the fracture(s) are suitable for management without a hard collar. There are no exclusions for other injuries (eg, fractured femur). Co-enrolment in other studies is permitted where this does not affect the DENS trial randomisation allocation or outcome measure assessment, and where this is not expected to burden the participant.

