### Randomisation and interventions

Web-based randomisation will occur with a minimisation algorithm based on:

Age at randomisation (<75 vs ≥75 years).Odontoid fracture type (I–III).^24^Frailty (CFS ≥5 vs <5).^23^

The first participant will be allocated to one arm with a probability of 0.5 and subsequent participants will be allocated with a probability of 0.8 to the group which minimises differences of the above variables between the two trial arms. Treatment allocation will be disclosed to the local research team via the web interface following randomisation.

The standard care arm will involve 12 weeks of hard collar treatment, following local usual choice of hard collar and local usual arrangements for collar care. For those allocated to the intervention (collar removal) arm, the collar will be removed as soon as possible, but may be weaned over several days if required for optimising analgesia. Removal of a collar prior to 12 weeks in the hard collar arm or wearing of a collar in the no collar arm will be recorded as a failure of adherence with explanation. Soft collars will not be used in either arm.

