### Outcome measures

The primary outcome measure is the EQ-5D-5L at 12 weeks postrandomisation.

Secondary outcome measures are:

Two and 6 weeks: EQ-5D-5L, Neck Disability Index (NDI), Neck Numeric Pain Scale.Twekve weeks: NDI, Neck Numeric Pain Scale, adverse events (AEs), compliance with hard collar use, analgesia use, length of hospital stay, discharge destination, bony fusion/stability on imaging, loss of muscle bulk in upper limbs using grip strength and bioimpedence.Six and 12 months: EQ-5D-5L, NDI, Neck Numeric Pain Scale, injury-related complications, mortality, health and social care visits/use, hospital admission or outpatient visits, health economics analysis.

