### Trial assessments

Assessments and timing of data collection are shown in table 1. Baseline data on demographics, comorbidities, injury, radiological findings and inpatient management will be recorded. Patient diaries will be used to collect pain scores, analgesia and collar use. Standard local clinical follow-up will occur. Research assessments will be carried out at 2, 6 and 12 weeks by the local research team and by a blinded member of the central research team at 6 and 12 months. Assessments will occur via telephone interviews, postal or online questionnaires, or during standard care appointments. A proxy can provide information on a patient’s behalf when required. Up to three reminder telephone calls will be made to maximise completion.

**Table 1 T1:** Timing of study assessments

	Timing from randomisation						
	Baseline	Discharge	2 weeks	6 weeks	12 weeks	6 months	12 months
Assessment							
Eligibility assessment	*						
Consent	*						
Demographics							
Baseline data	*						
CFS^23^	*						
Imaging							
Fracture type	X						
Imaging type	X				X		
Outcomes							
EQ-5D-5L			*	*	*	*	*
EQ-VAS			*	*	*	*	*
Neck Numeric Pain Scale			*	*	*	*	*
NDI			*	*	*	*	*
AEs		*			*		
Injury-related complications						*	*
Collar use		*	*	*	*		
Grip strength/bioimpedance	*				*		
Service use			*	*	*	*	*
Analgesia use			*	*	*		
Mortality					*	*	*

Assessments undertaken as standard care are shown with x. Study specific assessments are shown with*. Assessments may occur within the following time windows: 2 weeks (±1 week), 6 and 12 weeks (±2 weeks) and 6 and 12 months (±4 weeks). Fracture type refers to that of Anderson and D’Alonzo.^24^

EQ-5D-5L - EuroQol 5 dimension instrument 5 level version

AEs, adverse events; CFS, Clinical Frailty Scale; NDI, Neck Disability Index; VAS, Visual Analogue Scale.

At centres with facilities for routine assessment of grip strength and bioimpedence, all participants will be invited to take part in this arm of the study. Loss of muscle bulk in the upper limbs will be assessed over 12 weeks using hand grip strength measured with a dynamometer.^27^ Bioimpedence measurements will be made at the wrist and ankle. Muscle mass and skeletal muscle index as a marker of frailty will be calculated as per Janssen *et al.*^28^

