### Sample size

The recruitment target is 887 participants from around 25 UK sites over 2 years. An unadjusted sample size was calculated based on 90% power and a 5% significance level, using a two-sided two-sample t-test, for an effect size of 1/6 (0.05 minimum clinically important difference/0.3 SD) on the EQ-5D-5L at 12 weeks. This results in a sample size of 1514, increasing to 1893 assuming 20% missing data. This sample size can be reduced by accounting for correlation between baseline covariates (age, CFS) and 12 week EQ-5D-5L. It is anticipated that this correlation will be around 0.5, allowing a 25% reduction in sample size. Higher correlation will allow a larger reduction.^30^ Further, the postrandomisation measures of EQ-5D-5L at 2, 6 and 12 weeks, are assumed to have a serial correlation of 0.44 which allows a further 37.5% reduction in sample size.^30 31^ Including these reductions leads to the final target sample size of 887, with 1:1 allocation.

To check these assumptions, a sample size re-estimation will be modelled using a simulation approach based on 12 week outcome data from the first 300 participants.^30^ Due to the conservative assumptions made, particularly the assumed SD, the probability of increasing the sample size is small, and there is a larger probability it can be reduced.

Based on audits in two UK neurosurgical units, and assuming a 50% recruitment rate with staggered site opening, the target recruitment rate is 1.6 patients per site per month. An internal pilot will assess recruitment feasibility, targeting 132 patients (15% total) across 18 centres in 9 months. Progression criteria for the pilot are shown in table 2.

**Table 2 T2:** Study progression criteria

	Category		
	Red	Amber	Green
Total no recruited	≤108	109–131	≥132
Recruitment threshold (%)	≤82	83–99	100
Recruitment rate (patients per site per month)	1.07	1.33	1.63
No of sites open	<5	5–10	>10
Adherence failure	>20%	11%–20%	≤10%

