### Data analysis plan

The primary data analysis will be by intention to treat. A 5% two-sided significance level will be used throughout. A detailed statistical analysis plan will be developed by the study statisticians and finalised prior to locking of the trial database.

Analysis of the primary outcome will be a repeated measures analysis of covariance, including terms for treatment arm and the EQ-5D-5L responses at 2, 6 and 12 weeks. Adjustments will be made for the variables included in the randomisation minimisation algorithm. Adjustment for study site will be included as a random effect, if appropriate. The repeated measures approach enables estimation of an intervention effect at week 12 postrandomisation (primary outcome), and an overall assessment of the effect of the intervention over the 12-week period.

The 12-week NDI and Visual Analogue Scale will be analysed in a similar manner to the EQ-5D-5L. It is anticipated that results will underpin any between group differences seen in EQ-5D-5L, confirming and strengthening the clinical interpretation of the findings. All other secondary outcomes will be analysed with statistical models appropriate to the distribution of the outcome (see table 3). Where there are data recorded on multiple occasions postrandomisation, we may use an appropriate repeated measures model. Exploratory subgroup analyses by fracture type (I, II and III),^24^ CFS (<5 vs ≥5)^23^ and age (<75 vs ≥75 years) will be performed. The influence of any missing data on the robustness of the findings will be examined, for example, using multiple imputation models under a missing at random assumption. Screening logs will be analysed to assess generalisability of results.

**Table 3 T3:** Possible methods of analysis

Variable	Hypothesis	Outcome measures	Analysis methods
Baseline data	No difference between groups	Gender, age, comorbidities, injury data, radiological findings, inpatient management, CFS	Categorical variables: absolute numbers and percentages. Continuous variables: mean, median, SD, IQR.
Primary outcome			
Health-related quality of life at 12 weeks	Clinically important difference between two groups with early collar removal superior	EQ-5D-5L (continuous)	Repeated measures analysis of covariance at 2, 6 and 12 weeks, adjusting for minimisation variables
Secondary outcomes			
Pain	No difference between groups	NPRS (ordinal)	Ordinal regression

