A 12-month within trial health economic analysis will be undertaken based on National Institute for Health and Care Excellence (NICE) reference case recommendations to maximise UK policy relevance.^33^ This will include: adoption of a National Health Service (NHS) and Personal Social Services decision perspective; cost-utility approach for primary analysis (results presented in terms of incremental cost per quality-adjusted life year (QALY), derived from EQ-5D-5L data with an area under the curve approach, omitting baseline); discount rate of 3.5% for both costs and QALYs (where applicable); and use of probabilistic sensitivity analysis, to generate cost-effectiveness acceptability curves via the recycled predictions technique.^33 34^ Choice of primary analysis cost per QALY threshold and EQ-5D-5L scoring algorithm will match NICE preferences at the time of data lock. Resource use will be combined with standard UK price weights to generate costs.^35 36^ The latest financial year for which at least one study participant provides data and prices are available will be selected as base year. Univariate mean QALYs, resource use and costs will be presented for each trial arm alongside differences in means and associated 95% CIs. Multivariate analysis of both QALYs and total costs, will also be presented controlling for baseline costs where available and minimisation variables. Missing data will be imputed using appropriate techniques depending on degree of missingness, likely multiple imputation by chained equations.

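### Patients with other low-impact injuries are eligible and no baseline EQ-5D-5L is taken, yet other injury is not a named covariate: a cheap gain in precision left unused, not an error

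*Protocol article*

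**What the plan says.** Under Exclusion criteria, the protocol article states: "There are no exclusions for other injuries (eg, fractured femur". Limits apply all the same. The injury must be low impact, high-impact injuries are excluded, patients not expected to survive to discharge are excluded, and an additional cervical fracture must be suitable for management without a collar.

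Under Outcome measures: "The primary outcome measure is the EQ-5D-5L at 12 weeks postrandomisation". Table 1 schedules the EQ-5D-5L from 2 weeks onwards and not at baseline. The health economic text in the Data analysis plan is consistent with this, with QALYs "derived from EQ-5D-5L data with an area under the curve approach, omitting baseline".

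The primary analysis is a repeated measures analysis of covariance over 2, 6 and 12 weeks. On covariates the Data analysis plan says: "Adjustments will be made for the variables included in the randomisation minimisation algorithm". Under Randomisation and interventions those variables are: "Age at randomisation (<75 vs ≥75 years).Odontoid fracture type (I–III).^24^Frailty (CFS ≥5 vs <5).^23". For site: "Adjustment for study site will be included as a random effect, if appropriate". Other injury is not a minimisation factor, a named covariate or a subgroup.

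On what is collected, Trial assessments says: "Baseline data on demographics, comorbidities, injury, radiological findings and inpatient management will be recorded". Table 3 likewise lists injury data among the baseline variables. Neither place says that injuries other than the neck fracture are captured as a separate item.

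**The concern.** A patient with a fractured femur and an odontoid fracture will probably report worse EQ-5D-5L scores at 2, 6 and 12 weeks than a patient with the neck fracture alone, in either arm. In many quality-of-life trials a baseline score would take up part of that difference. Here there is none, and the named covariates do not describe other injuries, so the difference stays in the residual variance.

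Two things are at stake, both limited. One is precision: a prognostic variable outside the model makes the standard error larger than it need be. The other is the conditional effect of chance imbalance: if more patients with other injuries fall in one arm, the estimate from that one trial moves with them. The plan already looks to baseline covariates for efficiency, since it takes a 25% sample-size reduction from age and frailty, so a further prognostic covariate fits its approach.

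**Working it through.** **Reproducing the plan's figure.** The inputs come from the Sample size section: "An unadjusted sample size was calculated based on 90% power and a 5% significance level, using a two-sided two-sample t-test", difference 0.05, SD 0.3, 20% missing data, correlation 0.5 with age and CFS, and a further 37.5% reduction for repeated measures.

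- Per arm: 2 × (1.960 + 1.282)² × 0.3² / 0.05² = 757, so 1514 in total.
- Missing data: 1514 / 0.8 = 1892.5, rounded up to 1893.
- Covariates and repeated measures: 1893 × (1 − 0.5²) × (1 − 0.375) = 887.3.

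The target of 887 reproduces.

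**Planning variance and power.** These reductions imply a variance of 0.09 × 0.75 × 0.625 = 0.0422. The number analysed is 887 × 0.8 = 709.6, or 354.8 per arm. The standard error is √(2 × 0.0422 / 354.8) = 0.0154, and power is Φ(0.05 / 0.0154 − 1.96) = 90.0%.

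**Effect of the extra covariate.** Let p be the proportion with another injury and d the EQ-5D-5L deficit. Neither is in the documents, so the values below are assumptions. Taking the deficit as constant over visits and independent of age and CFS, adjustment removes variance v = p(1 − p)d².

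| p | d | v | v / 0.0422 | Power after adjustment | Equivalent total N |
|---|---|---|---|---|---|
| 10% | 0.05 | 0.0002 | 0.5% | 90.2% | 882 |
| 20% | 0.10 | 0.0016 | 3.8% | 91.1% | 853 |
| 30% | 0.15 | 0.0047 | 11.2% | 93.1% | 788 |
| 40% | 0.20 | 0.0096 | 22.8% | 95.8% | 685 |

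Equivalent N is 887 × (1 − v / 0.0422).

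**Sensitivity to the variance used.** The 37.5% reduction is close to what averaging three visits with serial correlation 0.44 would give, since (1 + 2 × 0.44) / 3 = 0.627. Whether it carries over to a week-12 contrast is a separate question. If the repeated measures added nothing at week 12, the residual variance would be 0.09 × 0.75 = 0.0675. The mid-case saving would then be 0.0016 / 0.0675 = 2.4%, and the full range 0.3% to 14.2%.

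**Chance imbalance.** The SD of the between-arm difference in prevalence is √(2p(1 − p) / 354.8). In the mid case this is 0.030, so a 1-SD imbalance shifts the estimate by 0.10 × 0.030 = 0.003, or 6% of the 0.05 target difference. At 1.96 SD the shift is 0.006, or 12%. Over the whole assumed range the shift is 0.001 to 0.007 at 1 SD and 0.002 to 0.014 at 1.96 SD.

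**The case against.** The strongest reply is that nothing is wrong. Adjusting for the minimisation variables is a standard and valid choice, and the article applies it consistently. The sample size claims no gain from other injury, and its SD of 0.3, which the article regards as conservative, may already include this variation. Comorbidities or sex could be proposed as covariates on the same reasoning. A detailed analysis plan is still to come and may widen the set. The gain rests wholly on assumed inputs.

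Most of this stands, and it rules out four stronger readings that a reader might draw.

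- **The primary estimate is biased.** It is not. Randomisation keeps it unbiased, and the confidence interval already allows for chance imbalance in unadjusted factors.
- **The variable is already in the database.** The article lists injury only as a category of baseline data, which may mean the neck injury and its mechanism.
- **Polytrauma is admitted without limit.** The low-impact requirement and the other exclusions remove much of the severe trauma that would produce large deficits.
- **The top of the range is the expected gain.** It needs 40% prevalence and a deficit of 0.20, four times the trial's minimum important difference, both at once. Any correlation of other injury with age or frailty shrinks the gain.

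The objection does not remove the suggestion. The article itself names the covariate set for the primary model, and without a baseline EQ-5D-5L no other term stands in for concurrent injury. That separates this variable from the general run of candidates.

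**Conclusion.** The point holds as a minor, inexpensive improvement to the analysis. It does not correct an error, and 887 is not put in doubt. Eligibility admits other low-impact injuries, the outcome is generic and unmeasured at baseline, and the stated model has no term for those injuries.

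The likely benefit is about one percentage point of power, or about 4% of the sample, at 20% prevalence and a deficit of 0.10. The range is 0.2 to 5.8 points over prevalences of 10–40% and deficits of 0.05–0.20. These figures assume that other injury is independent of age and CFS, that its effect is constant over visits, and that the plan's variance assumptions hold. The documents can neither confirm nor narrow them.

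**What to change.** 1. Confirm that the baseline injury data record other acute fracture or major injury separately from the odontoid fracture, and write a definition that all sites can apply in the same way.
2. Before database lock, pre-specify it as a yes/no covariate with its interaction with visit in the primary repeated-measures model, and likewise in the NDI and EQ-VAS models.
3. Leave eligibility, minimisation and the sample size as they are.

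The cost is three extra parameters (one main effect and two visit interactions) with about 710 participants analysed, plus agreement on the definition. If the item is not yet collected, one field must be added to the baseline form. Fixing the covariate in advance matters because adding it after results by arm are known would look data-driven.
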